#### Exploratory efficacy parameter (Translational Research)

Tumor tissues, circulation tumor cells, skin biopsies and blood cells and other blood based markers such as cell-free DNA and proteins or immune-associated molecules will be characterized. The biomarker expressions are planned to be correlated with tumor staging and response to therapy in both treatment arms. Available details of the translational analysis will be laid down in the SAP prior to performing the analysis.

Translational research analysis will be conducted by members of the translational research committee outside of ClinAssess.

### **8.4.4 Safety Evaluation**

#### Adverse events

Adverse event reported terms (as documented by the study investigator) and coded terms will be reviewed and re-coded if necessary. All information recorded such as onset date, stop date, duration, maximum intensity, seriousness, relationship to study drug and outcome will be listed.

Adverse event tables will be created. These tables will present the total number of patients reporting at least one specific event and the maximum CTCAE grade. Thus, patients reporting more than one episode of the same event will be counted only once by the worst CTCAE grade per patient.

Detailed adverse event tabulations consist of the number and percentages of patients involved per CTCAE Category and CTCAE Term, the highest relation to study drug, and the maximum severity.

Special tables will be displayed for CTCAE Grade III/IV/V adverse events. Additionally, analysis will be restricted to drug related adverse events and drug related CTCAE Grade III/IV/V events.

Furthermore, summary tables with patient identifications will be presented. These tables provide the numbers and percentages of patients with adverse events stratified by CTCAE category, CTCAE term and CTCAE grade, and also include the subject identification in the table.

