| Randomization procedure                               | 
Permuted block randomization will be applied to guarantee balanced group numbers throughout enrollment period. To increase homogeneity between treatment arms, randomization will be stratified by
 
 
1. Response to induction therapy at time of randomization (CR/PR vs. SD)
 
2. Prior oxaliplatin-containing adjuvant therapy (yes vs. no)
 
3. Planned starting dose of panitumumab for maintenance therapy, if patient will be assigned to arm A (full dosage vs. reduced dosage)
 
 
Randomization will be performed in the subgroup of patients achieving CR, PR or SD 12 weeks after start of induction therapy qualifying for maintenance treatment and re-induction treatment with all potential drug components.
                                                                                                                                                                                                                                           |
| Statistical considerations
Sample size calculation | 
With a total number of 218 events (progressions or death, whichever occurs first), a logrank test for testing superiority of progression-free survival with a 10% one-sided significance level will have 80% power to reject the null-hypothesis if the true median progression-free survival times in patients treated with maintenance alone and maintenance plus panitumumab are 7.5 and 10 months, respectively. A total of approx. 400 patients eligible for induction therapy should be accrued for randomisation of 272 patients needed to reach the required number of events.
                                                                                                                                                                                                                                                                                                                                                                                                                                                 |

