More treatment-related adverse events occurred in the wild-type KRAS subset compared with the mutant KRAS subset, presumably due to the longer therapy. Subjects in the wild-type KRAS subset received a higher number of panitumumab infusions compared with subjects in the mutant subset (mean [median] 10.0 [8.0] and 4.9 [4.0], respectively). These adverse events were mainly skin toxicities (erythema, pruritus, dermatitis acneiform) likely reflecting the increased duration of exposure to panitumumab. No qualitative differences in overall adverse events were observed between the wild-type KRAS subset, the mutant KRAS subset and the overall population, however, treatment related grade 3 adverse events were reported for 25% of subjects in the wild-type KRAS subset compared with 12% of subjects in the mutant KRAS subset. 2% of wild-type KRAS subjects and 1% of mutant KRAS subjects withdrew for panitumumab-related events.

The clinical safety profile of panitumumab in combination with chemotherapy is based on results from 9 clinical studies with data from 1536 subjects, including 585 subjects who received panitumumab in combination with oxaliplatin-based chemotherapy. The safety data of the pivotal phase III trials indicate a tolerable safety profile for panitumumab when administered in combination with oxaliplatin to subjects with wt KRAS mCRC as first-line treatment. In subjects treated with oxaliplatin, the rate of grade 3 and 4 adverse events and serious adverse events was slightly higher for panitumumab plus chemotherapy relative to chemotherapy alone, primarily due to toxicities known to be associated with panitumumab, such as rash, diarrhea, acneiform dermatitis and hypomagnesemia. However the rate of discontinuation was similar between treatment arms, suggesting that these events were clinically manageable.

Please refer to the current version of the panitumumab Investigator's Brochure as well as the updated safety information contained in the Investigational New Drug safety letters for further updates.

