### **2.2 Secondary Objectives**

To compare maintenance arms with respect to:

- Time from randomization until failure of treatment strategy (death/ progression)
- Progression-free survival from re-induction
- Objective response after 12 weeks of induction chemotherapy
- Objective best response during maintenance and re-induction
- Overall survival measured from time of randomization and from time of registration
- Safety
- Health and skin related Quality of life

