### 8.2 Sample Size Calculation

The sample size required within this trial is calculated based on the hypothesis system described in section 8.1. To estimate the number of events (progressions or deaths, whichever first) required within the Full Analysis Population in this study, the following assumptions are made:

- One-sided Log-rank test will be applied for comparison of PFS between treatment arms.
- The one-sided significance level is set to 10%. This reflects the goal of the phase II to
  - allow for unbiased evaluation of any potential superiority of 5-FU/FA plus panitumumab compared to 5-FU/FA alone
  - generate sufficient data for preliminary assessment of the clinical relevance of the maintenance treatment with 5-FU/FA plus panitumumab
  - provide a sensible gate-keeper for further development and
  - support further decision making within the community and
  - last but not least decide whether a Phase III trial is justified.
- Progression-free survival follows an exponential distribution.
- Median PFS in patients treated with maintenance lacking panitumumab is expected to be roughly 7.5 months. This is derived by considering OPTIMOX2 showing a median PFS of 8.6 months in patients treated with mFOLFOX7 during induction followed by simplified LV5FU2 therapy thereafter. Excluding the first 3 months of induction therapy and excluding progressions and other cases where patients are not eligible for randomization after 3 months which do not start maintenance therapy, will lead to a median progression-free survival (calculated from date of randomisation) of roughly 7.5 months.

- On the other hand, previous phase III studies (e.g., PRIME-study) have shown that adding panitumumab can lead to prolongation of PFS with hazard ratios (HR) ranging between 0.7 and 0.8. Based on this data, 5-FU/FA+panitumumab will be considered to be clinically relevant if it is associated with a HR of 0.75; this converts into a median PFS of 10 months.
- The power to yield statistical significance if the HR is in fact 0.75 is set to 80%.
- All patients are to be followed until progression or death whatever occurs first. 5% of patients will be assumed to be continuously lost during the study period per year.

Based on the assumptions above, a logrank test for comparing the progression-free survival curves will have 80% power to reject the null-hypothesis if the true hazard ratio is 0.75 with a total number of 218 events (progressions or deaths, whichever occurs first).

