## **8.4 Methods of Statistical Analysis**

### **8.4.1 General Statistical Considerations**

The statistical evaluation will be carried out by ClinAssess GmbH. Statistical analysis is based on the International Conference on Harmonization (ICH) Guidelines “Structure and Content of Clinical Study Reports” and “Statistical Principles for Clinical Trials”.

Data will be analyzed using the SAS software package version 9.4 or higher on the Windows platform.

Study-specific SAS programs will be written for individual patient data listings and for aggregated analyses of adverse events and laboratory values. The biometrical analysis will be accompanied by the appropriate internal quality control according to ClinAssess’s current SOPs. The data analysis will be performed according to the statistical analysis plan (SAP) which will be finalised prior to database lock and prior to any statistical analysis. Any changes to the statistical analysis planned in the protocol are to be justified and documented in the SAP if they were decided before database lock. Any changes made to the SAP after the database lock will be documented in the clinical study report.

All data recorded in the case report forms describing the sample, the efficacy and the safety will be analyzed descriptively. Categorical data will be presented in contingency tables with frequencies and percentages. Continuous data will be summarized with at least the following: frequency (n), median, quartiles, mean, standard deviation (standard error), minimum and maximum. Number of patients with protocol deviations during the study and listings describing the deviations will be provided.

In general, chi-square tests will be used to compare percentages in a two-by-two contingency table, replaced by Fisher’s exact test if the expected frequency in at least one cell of the associated table is less than 5. Stratified two-by-two contingency tables will be analyzed using Cochran-Mantel-Haenszel tests. Comparison of ordinal variables between treatment arms will be performed using the asymptotic Wilcoxon-Mann-Whitney test, replaced by its exact version in case of ordinal categories with small number of categories and/or sparse data within categories. Any shift in location of quantitative variables between study groups will be performed with Wilcoxon-Mann-Whitney tests as well.

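### Section 8.4.4 reports adverse events only as crude percentages of patients, which would overstate arm A's rate of steadily accruing events if panitumumab prolongs maintenance as the design assumes

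*Protocol*

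**What the plan says.** Protocol section 2.2 places safety under the heading "To compare maintenance arms with respect to". Section 8.3.3 defines the Safety Population as randomized patients who started maintenance, grouped by treatment received.

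Section 8.4.4 then gives the AE output: "These tables will present the total number of patients reporting at least one specific event and the maximum CTCAE grade". Each patient counts once, at worst grade. The tables for grade III to V and for drug-related events restrict the same count. Onset date, stop date and duration are to be listed, but no summary uses them. The general rule in section 8.4.1 is that "chi-square tests will be used to compare percentages in a two-by-two contingency table".

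Maintenance continues in both arms until progression (section 3.1.1), and AEs are assessed throughout treatment up to the end-of-treatment visit (section 5.1.3). The design expects the arms to differ in time to progression: in section 8.2 the hazard ratio of 0.75 is clinically relevant and "this converts into a median PFS of 10 months", against 7.5 months without panitumumab.

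**The concern.** A percentage of patients with at least one event depends on the event rate and on how long patients are watched. Here the watching time ends with treatment, and treatment ends mostly with progression, which is the primary endpoint. The better panitumumab works, the longer arm A is observed and the more arm A patients have time to record an event.

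The protocol uses this explanation itself. In section 1.1.3.2: "More treatment-related adverse events occurred in the wild-type KRAS subset compared with the mutant KRAS subset, presumably due to the longer therapy". Yet it plans no AE measure that would separate rate from duration. Section 8.2 describes the trial as a gatekeeper for further development and for the decision on a phase III trial. If the drug works, part of its benefit could be read as extra toxicity.

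**Working it through.** **Inputs from the protocol.** Synopsis: "the true median progression-free survival times in patients treated with maintenance alone and maintenance plus panitumumab are 7.5 and 10 months, respectively". Section 8.2: "Progression-free survival follows an exponential distribution"; loss of 5% of patients per year. Section 8.1: the hazard ratio is arm A over arm B.

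**Reproducing the plan's figure.** Schoenfeld's formula with 1:1 allocation, one-sided 10% and 80% power gives 4 × (1.2816 + 0.8416)² / (ln 0.75)² = 217.9, so 218 events, as stated. The medians and the hazard ratio are therefore used consistently.

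**Length of the maintenance window.** Exit hazard = ln 2 / median.
- Arm B: 0.0924 per month, mean 10.8 months.
- Arm A: 0.0693 per month, mean 14.4 months.
- Ratio: 14.4 / 10.8 = 1.33. With the planned 5% yearly loss in both arms it is 1.31.

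**Events with a constant hazard.** Assume the same first-event hazard L in both arms and a window that ends with maintenance. The crude proportion is L / (L + exit hazard). The values of L are assumptions.

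| L per month | Arm B | Arm A | Excess (points) | Relative risk |
|---|---|---|---|---|
| 0.02 | 17.8% | 22.4% | 4.6 | 1.26 |
| 0.05 | 35.1% | 41.9% | 6.8 | 1.19 |
| 0.10 | 52.0% | 59.1% | 7.1 | 1.14 |

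The excess is smaller at the extremes: 1.6 points when arm B is at 5%, and 4.2 points when it is at 80%.

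**Early-onset events.** Let the hazard L act only in the first T months. The crude proportion is L / (L + exit hazard) × (1 − exp(−(L + exit hazard) × T)). For L of 0.10 to 0.35 per month:
- T = 1: excess 0.1 to 0.3 points.
- T = 2: excess 0.4 to 0.9 points.
- T = 3: excess 0.7 to 1.6 points.

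The relative risk is 1.01 to 1.03 throughout, so the crude percentage is nearly fair here.

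**The same early-onset events per patient-month.** Time at risk to first event or exit is (1 − e) / (L + exit hazard) + e / exit hazard, with e = exp(−(L + exit hazard) × T). With T = 1 and L = 0.10, arm B has 0.0910 / 9.84 = 0.0092 and arm A 0.0920 / 13.10 = 0.0070 events per month, a ratio of 0.76. With T = 3 and L = 0.35 the ratio is 0.80. Arm A appears 20% to 24% less toxic although the hazards are equal, because its extra event-free months enter the denominator.

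**What shrinks the window ratio.**
- Pooling re-induction, with an assumed median of 3 to 5 months in both arms: ratio 1.24 to 1.20. The excess is 3.2 to 5.6 points when arm B's pooled percentage is 20% to 50%.
- Stopping all treatment before progression at the same hazard in both arms: at 0.02 or 0.04 per month the ratio is 1.26 or 1.21.
- Extra stopping of all treatment in arm A only: 0.0924 − 0.0693 = 0.023 per month, a quarter of arm A's exits, cancels the gap.
- A true hazard ratio of 1: ratio 1.00 and no excess.

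**The case against.** **The SAP may add exposure-adjusted summaries.** It may; it is not among the documents at hand, and section 8.4.1 says the analysis will follow it. But 8.4.4 does not leave the AE measure open. It names one, whereas the quality-of-life and laboratory parts expressly defer details to the SAP. The point is limited to that stated measure.

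**Safety is descriptive and no AE test is specified.** This stands. Section 8.4.4 names no test, the chi-square sentence in 8.4.1 is a general rule, and all tests other than the primary one are exploratory. A reader might compute how often a two-sided 5% test of AE percentages would reject falsely. The protocol prescribes no such test, so that figure would describe an analysis nobody has planned.

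**The signature toxicity is early.** This also stands. Section 1.1.3.2 gives a median of 10 days to first skin toxicity, section 6.5.3 puts the rash peak at weeks 4 to 6, and both arms receive panitumumab for 12 weeks before randomization. The 5 to 7 points do not apply to such events.

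**The crude percentage is a legitimate quantity.** It is the burden that a patient treated to progression would meet. That is why the tables should stay. It is not the whole answer to a comparison of toxicity between arms, and the protocol offers nothing beside it.

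**Stopping for toxicity may even out the windows.** Possibly, but stopping panitumumab alone need not end the window, since sections 6.3.1.5 and 6.3.2.4 let chemotherapy continue. Only reported exposure would show which case applies.

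**Conclusion.** The concern holds in a limited form. The only AE measure in 8.4.4 mixes event rate with duration of treatment, and the design expects duration to differ. Under the plan's exponential medians, equal constant event rates and a window that ends with maintenance, arm A's crude percentage is about 5 to 7 points too high for event rates of 2 to 10 per 100 patient-months. The excess is about 1 point for early-onset events, about 3 to 6 points with re-induction pooled under the assumed durations, less with earlier stopping in arm A, and nil at a hazard ratio of 1.

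A reader might infer that arm A will look more toxic across the board, or that the percentages should give way to rates per patient-month. The protocol supports neither reading. Its own account of skin toxicity describes early onset, where the crude figures are nearly fair and the rates would hide panitumumab's toxicity. The change is worth making but does not touch the primary analysis.

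**What to change.** Keep the crude tables and add to section 8.4.4, for AEs in the maintenance phase and by arm:

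1. Duration of maintenance exposure, with patient-months at risk.
2. Time to first event from the first maintenance dose, for any-grade events, grade III to V events, and the skin, gastrointestinal and magnesium events named in section 1.1.3.2. Give a cause-specific hazard ratio with confidence interval, censoring patients without the event at the end of the maintenance AE window, and cumulative incidence at common time points with end of maintenance as the competing event.

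The cause-specific hazard ratio is 1 under equal hazards for both the constant and the early-onset pattern. Exposure-adjusted rates per patient-month may be shown as a supplement, marked as unsuitable for comparing arms on early-onset events. All of these analyses stay exploratory.

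The cost is some wording and a few extra tables. AE start dates (section 7.4) and dose dates (section 6.2.1.4) are already recorded, so no new data, patients or visits are needed.

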#### Laboratory parameters

Quantitative laboratory parameters will be evaluated stratified by treatment arm and visit. For each parameter, the distribution over time as well as the mean values at baseline and changes from baseline will be computed for each treatment arm and reported with descriptive statistics.

Values outside normal ranges will be listed. Any statistical test will be interpreted on an exploratory perspective only. Laboratory parameters to be included in this analysis will be detailed in the statistical analysis plan.

Safety analyses will be conducted for the Safety Population. However, additional tables showing the incidence of adverse events during induction therapy will be presented for all patients enrolled with documented start of induction therapy.

### **8.5 Interim and Final Analysis**

No confirmatory interim analyses for efficacy with the aim to stop the trial prematurely due to proof of efficacy or futility are foreseen within the study protocol.

The primary confirmatory statistical analysis of this trial is performed whenever at least 218 events (first progressions/deaths) are documented within the Full Analysis population. The final analysis will be performed with a minimum follow-up of 2 years after randomization of the last subject available for each patient randomized to the trial.

## **9 Data Quality Assurance**

The overall procedures for quality assurance of clinical study data are described in the Standard Operational Procedures of ClinAssess. Accurate and reliable data collection will be assured by verification and cross-check of the electronic CRFs against the investigator's records by the study monitor (source document verification), and the maintenance of a drug-dispensing log by the investigator. Data for this study will be recorded via electronic Case Report Forms. It will be transcribed by the site from the source documents onto the electronic CRF. Data are reviewed and checked for omissions, apparent errors, and values requiring further clarifications using computerized and manual procedures. Data queries requiring clarification are communicated to the site for resolution. Only authorized personnel will make corrections to the clinical database and an audit trail will document all corrections.

## **10 Study Committees – Data Safety Monitoring Board**

A Data Safety and Monitoring Board will be established, consisting of three experts in medical oncology, gastrointestinal cancer surgery and/or biostatistics.

The DSMB will receive regular information on safety results of the trial, namely a list of reported SAEs/SUSARs. Details on the work of the board will be described in a specific DSMB charter, to be jointly agreed upon by the board and the sponsor.

## **PART II – ETHICS AND GENERAL STUDY ADMINISTRATION**

### **11 Ethical Aspects**

#### **11.1 Declaration of Helsinki / Good Clinical Practice**

The Declaration of Helsinki is the accepted basis for clinical study ethics, and must be fully followed and respected by all those engaged in research on human beings. Any exceptions must be justified and stated in the protocol. The latest version of the Declaration of Helsinki is available at [www.wma.net](http://www.wma.net).

Additionally it is the responsibility of all those engaged in research on human beings to ensure that the study is performed in accordance with the international standards of Good Clinical Practice and according to all local laws and regulations concerning clinical studies.

#### **11.2 Patient Information and Informed Consent**

It is the responsibility of the investigator to obtain written informed consent from each patient participating in this study, after an adequate explanation of the aims, importance, anticipated benefits, potential hazards and consequences of the study according to applicable local laws. Written informed consent must be obtained before any study-specific procedures are performed. It must be also explained to the patient that they are completely free to refuse to enter the study or to withdraw from it at any time, for any reason, without incurring any penalty or withholding of treatment on the part of the investigator.

With the declaration of consent, the patient agrees to data about his/her disease being recorded within the context of the clinical trial and that it may be transferred to the sponsor in pseudonymized form.

The subject/patient also agrees to allow the monitor/auditor/health authorities to verify the patient data collected against the subject's/patient's original medical records for the purpose of source data verification.

The informed consent form personally signed and dated by the patient must be kept on file by the investigator(s) and documented in the CRF and the subject's medical records. The investigator must confirm with the sponsor that he/she has obtained written informed consent.

If new safety information results in significant changes to the risk/benefit assessment, the consent form should be reviewed and updated if necessary. All patients (including those already being treated) should be informed of the new information and must give their written informed consent to continue in the study.

If family doctors are to be informed of their patients' participation in the clinical study, this should be mentioned in the consent form.

